| Plan for addressing confounding Age and sex will be adjusted for in all analyses as potential confounders of associations between ethnicity and prescribing. The potential mediating influences of smoking, BMI, polypharmacy, multimorbidity, patient adherence, patient engagement, diabetes duration and HbA1c will be quantified by adjusting regression models for each of these variables in turn. |
| Plans for addressing missing data Monitoring and treatment of type 2 diabetes is incentivised by the UK’s primary care Quality Outcomes Framework (QOF), therefore recording of cardiovascular risk factors and some other of the covariates mentioned above is likely to be more complete than for other disease areas. Where these factors are missing, we will use complete case analysis as data may not be missing at random.  Missing ethnicity data is the chief concern. Given that ethnicity data are unlikely to be missing at random, multiple imputation methods are not appropriate, and we will perform complete case analysis instead. Complete case analysis will be unbiased if missingness is independent of the outcome, conditional on model covariates. One of the main reasons that missingness would be expected to be associated with prescribing patterns is that people who are poorly engaged with their GP may be less likely to have ethnicity recorded (whatever their ethnicity), or be eligible to be prescribed medication. However, as discussed above we plan to adjust for number of consultations in the year prior to diagnosis. Within those with similar levels of GP contact prior to diabetes diagnosis, it is less conceivable that missingness of ethnicity will be strongly associated with prescribing patterns. Additionally, three sensitivity analyses (see section N) will be performed to boost ethnicity recording. |
| Patient or user group involvement (if applicable) A study steering group will be convened consisting of the collaborators and several people with type 2 diabetes, ideally representing each ethnic group. These individuals will be recruited from the pool of participants from the SABRE study (Southall and Brent Revisited, PI: NC) and will meet annually to discuss the study progress, results and dissemination of findings. Key results will be reported via the media, Diabetes UK website, Living with Diabetes events and “Balance” magazine (for Diabetes UK members), to make people with diabetes aware of the findings. |

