| N. Exposures, outcomes and covariates *Data sources are listed in square parentheses*  Exposures:  For all objectives, the exposure is either South Asian or African Caribbean ethnicity (defined as above), with European ethnicity as the baseline category. *[Primary care clinical records]*  Health Outcomes by study objective:   1. Proportion of those eligible for primary prevention who are prescribed a) antihypertensives and b) lipid-lowering medication *[Primary care clinical records, prescription drug files]* 2. Time to first anti-diabetic/ antihypertensive/ lipid-lowering medication prescription. *[Primary care clinical records, prescription drug files.]* 3. Choice of a) anti-diabetic (first- to third-line), b) antihypertensive and c) lipid-lowering medications, see appendix for code lists for each (derived from chapters of the British National Formulary). *[Prescription drug files.]* 4. Doses used for each a) anti-diabetic, b) antihypertensive and c) lipid-lowering medication. *[Prescription drug files.]* 5. Monitoring rate, stratified by the time since treatment initiation, e.g. the number of a) HbA1c, b) BP or c) lipid measures divided by the amount of person time, within strata of time since initiation (i.e. first year, second year since initiation etc). *[Prescription drug files, test records.]* 6. Time to treatment intensification after detection of sub-optimal risk factor control. *[Primary care clinical records, prescription drug files, test records.]* Sub-optimal control will be classified as follows:    1. Diabetes; HbA1c≥53mmol/mol (7.5%) (7)    2. Hypertension; blood pressure≥140/80 mmHg, or 130/80 mmHg in those with neuropathy/ nephropathy or retinopathy (24)    3. Lipids; <40% reduction in non-HDL cholesterol (25) 7. Influence of the following on associations between ethnicity and prescribing: smoking, BMI, deprivation, polypharmacy, multi-morbidity, drug adherence (for outcomes iv) and v)), patient engagement with healthcare, diabetes duration and HbA1c. *[Linked IMD data, primary care clinical records, prescription drug files, test records.]*   Covariates (all taken from last entry in medical notes prior to follow-up time commencing)  Age *[Primary care clinical records]*  Sex *[Primary care clinical records]*  Smoking status *[Primary care clinical records]*  BMI *[Primary care clinical records]*  Deprivation (using patient-level IMD scores, with sensitivity analyses using practice-level IMD scores) *[Primary care clinical records, linked deprivation data]*  Polypharmacy (number of medications) *[Prescription drug files]*  Multimorbidity (defined by presence or absence of the following key co-morbidities: coronary heart disease, cerebrovascular disease, heart failure, atrial fibrilliation, hypertension, chronic kidney disease, peripheral arterial disease, retinopathy, neuropathy, cancer [any], COPD/ asthma, severe mental illness) *[Primary care clinical records]*  Patient engagement/ access (using the number of consultations in the year preceding diabetes diagnosis as a proxy) *[Primary care clinical records]*  Patient adherence (using the proportion of days covered: PDC=days of medication supplied per x day period/ x (27)). This will be calculated separately for all medications issued over the follow-up time of interest, and then a mean PDC for all medications will be derived for each patient. Both measures are important as adherence may vary by drug. *[Prescription drug files]*  Disease parameters: baseline HbA1c/ blood pressure and number of years since diabetes diagnosis *[Primary care clinical records, test records.]* |

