| O. Data/ Statistical Analysis For all parts of the study, the population will be people with and without new-onset type 2 diabetes active in CPRD from 2006 (see section K, above) and the exposure will be ethnicity (either South Asian vs. European [baseline] or African Caribbean vs. European [baseline], as detailed in section L, above). Covariates in base models will include age and sex, and further covariates will be considered individually, as outlined in section vi) below. Statistical analysis is further considered by objective:   1. **Outcome:** Proportion of those eligible for primary prevention who are prescribed a) antihypertensives and b) lipid-lowering medication   **Entry:** Date of incident a) hypertension Read code/ raised BP reading or b) elevated 10 year CVD risk score, at least 12 months after study start date of 1^st^ January 2005  **Exit:** First of; date of first antihypertensive/ lipid-lowering medication prescription (defined by the absence of a prescription for the medication in the previous 6 months’ records), end of study, leaving CPRD practice or death  **Analysis:** Proportions receiving antihypertensives/ statin will be compared by ethnicity, then logistic regression models will be used to adjust for confounding/ investigate potential mediators  **Example effect measure:** Odds ratio (OR) of receiving an antihypertensive/ lipid-lowering medication vs. not for each ethnic group of interest, stratified by time period since identification of hypertension/ elevated CVD risk   1. **Outcome**: time to initiation of first-line anti-diabetic/ antihypertensive/ statin, probability of receiving anti-diabetic/ antihypertensive/ statin at one year post-diagnosis/ identification of high CVD risk   **Entry**: date of type 2 diabetes diagnosis/ incident hypertension Read code or raised BP reading/ incident high 10 year CVD risk score recording  **Exit**: date of first anti-diabetic/ antihypertensive/ statin prescription (defined by the absence of a prescription for the medication in the previous 6 months’ records), or end of study/ leaving CPRD practice/ death  **Analysis**: summary statistics will be compared by ethnicity using Kaplan-Meier time-to-event analysis (cumulative failure probability in a given time frame by ethnicity, comparison of medians by log-rank test), Cox proportional hazards regression models will be used to adjust for confounding/ investigate potential mediators  **Example effect measure**: hazards ratio (HR) for anti-diabetic/ antihypertensive/ statin prescription   1. **Outcome:** proportions of patients prescribed medication from each anti-diabetic (stratified by first- to third-line treatment), antihypertensive and lipid-lowering class (defined by the absence of a prescription for the medication in the previous 6 months’ records)   **Sub-population:** a) all participants starting first- to third-line anti-diabetic treatment, b) all patients on antihypertensives, or c) all patients on lipid-lowering medication  **Analysis:** proportions receiving each drug will be compared by ethnicity, then logistic regression models will be used to adjust for confounding/ investigate potential mediators  **Example effect measures**: odds ratio (OR) of being prescribed metformin (=1) vs. non-metformin medication (=0) at first stage of treatment, OR of being prescribed sulphonylurea (=1) vs. non- sulphonylurea medication (=0) at second stage of treatment, OR of calcium-channel blocking antihypertensive prescription vs. non- calcium-channel blocking antihypertensive in those on antihypertensive treatment, OR of statin prescription vs. non-statin lipid-lowering medication prescription in those with >10% 10 year cardiovascular risk   1. **Outcome:** proportions of patients prescribed each dose of each anti-diabetic, antihypertensive and lipid-lowering medication, stratified by treatment stage (defined by the absence of a prescription for the medication in the previous 6 months’ records)   **Sub-population:** a) all participants on first- to third-line anti-diabetic treatment, b) all patients on antihypertensives, or c) all patients on lipid-lowering medication  **Analysis: :** proportions receiving each dose of each drug will be compared by ethnicity, then logistic regression models will be used to adjust for confounding/ investigate potential mediators  **Example effect measures**: OR of being prescribed maximum dose (2g daily) vs. sub-maximum dose of metformin, OR of being prescribed atorvastatin 10mg per day vs. higher doses (20mg, 40mg or 80mg)   1. **Outcome:** yearly monitoring rate post commencement of medication from each anti-diabetic (first- to third-line), antihypertensive and lipid-lowering class – i.e. number of times HbA1c/ blood pressure/ blood lipids measured per person-year of follow-up, stratified by year after commencement; may be multiple entry dates per person for different medications   **Entry:** first use of any medications of interest from 2006 onwards  **Exit:** first of; end of strata (e.g. 1 year after medication commencement), end of study/ leaving CPRD practice/ death  **Analysis:** summary statistics will be compared by ethnicity, Poisson regression modelling used to adjust for confounding/ investigate potential mediators  **Example effect measures**: yearly monitoring rate ratios (RRs)   1. **Outcome:** time to medication intensification (up-titration, addition or switching) after detection of sub-optimal control of diabetes, hypertension or blood lipids, or probability of intensification 1 year post-detection of sub-optimal control; may be multiple entry dates per person for different medications   **Entry:** date when sub-optimal risk factor control detected (see section M for how this is defined for each risk factor)  **Exit:** first of; date of anti-diabetic, antihypertensive or lipid-lowering treatment intensification, end of study/ leaving CPRD practice/ death  **Analysis:** summary statistics will be compared by ethnicity using Kaplan-Meier time-to-event analysis (cumulative failure probability in a given time frame by ethnicity, comparison by log-rank test), Cox proportional hazards regression models will be used to adjust for confounding/ investigate potential mediators  **Example effect measures**: cumulative failure probability for each ethnic group 1 year post detection of sub-optimal value, comparison of median survival times using the log-rank test by ethnicity, HRs of intensification stratified by year   1. **Outcome:** influence of deprivation, polypharmacy, multi-morbidity, drug adherence (iv) and v) only), patient engagement with healthcare, diabetes duration and HbA1c on any ethnic differences found in i) to v).   **Entry:** as above for i), iv) and v)  **Exit:** as above for i), iv) and v)  **Analysis:** as above for i) to v)  **Covariates:** smoking status, BMI, deprivation, polypharmacy, multi-morbidity, drug adherence, patient engagement with healthcare, diabetes duration and HbA1c  **Effect measures:** we will observe the degree of attenuation of the ethnic difference effect measure for each outcome when each covariate is inserted in turn to models, and thus evaluate the likelihood of confounding or mediation  Sub-group/ sensitivity analyses  See section O of original application  Plans for addressing misclassification and bias  See section O of original application  Multiple comparisons  See section O of original application |

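### The complete-case argument for missing ethnicity relies on a consultation adjustment that the base models omit and that, as defined, cannot be computed for people without diabetes

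*Supplement*

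**What the plan says.** The original application's section on missing data calls missing ethnicity the chief concern, rejects multiple imputation because the data are unlikely to be missing at random, and adopts complete-case analysis. The stated condition is that "Complete case analysis will be unbiased if missingness is independent of the outcome, conditional on model covariates". The threat it names is that "people who are poorly engaged with their GP may be less likely to have ethnicity recorded (whatever their ethnicity"), and may also be less likely to be eligible for medication. Its modelling answer is that "we plan to adjust for number of consultations in the year prior to diagnosis". The next sentence shows that diabetes diagnosis is meant: "Within those with similar levels of GP contact prior to diabetes diagnosis", it says, a strong association between missing ethnicity and prescribing is less conceivable. The limitations section leans on this argument when it expects no serious bias.

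The amendment of 9 December 2019 has no revised missing-data section, so this is the only argument on file. Its section O says: "Covariates in base models will include age and sex, and further covariates will be considered individually, as outlined in section vi) below". The section on confounding agrees: age and sex go into all analyses, and engagement is one of several potential mediators added in turn.

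The amendment also extends the study to people without diabetes, who enter at an incident hypertension code or raised blood pressure reading, or at an elevated 10-year CVD risk score. Section N still defines the covariate as "Patient engagement/ access (using the number of consultations in the year preceding diabetes diagnosis as a proxy").

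**The concern.** The plan makes the validity of its complete-case analysis conditional on what is in the model, then leaves the variable it relies on out of most of the models. For the cohorts without diabetes, the variable has no date to count back from.

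The plan expects ethnicity to be recorded more often for minority patients, and expects engagement to affect both recording and prescribing. If engagement drives recording more strongly in Europeans than in minority groups, recorded Europeans will be a more engaged subset than recorded South Asian or African Caribbean patients. A comparison that does not condition on engagement would then show an ethnic difference in prescribing produced by who has a code. Differences of that kind are what the study sets out to report.

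**Working it through.** **1. Which analyses meet the plan's own condition**

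| Analysis | Consultations in the model? |
|---|---|
| Kaplan-Meier, log-rank, crude proportions and rates | No |
| Base model (age, sex) | No |
| Age, sex and one other covariate (smoking, BMI, deprivation and so on) | No |
| Age, sex and engagement, diabetes cohorts | Yes |
| Age, sex and engagement, cohorts without diabetes | Undefined: no diabetes diagnosis date |

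**2. Scale of the missingness**

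The plan states no bias figure to reproduce. Its counts do rest on 50% recording: 280K × 0.5 = 140K first-line starters, of whom 0.86 × 140K = 120.4K are European, as stated.

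**3. Illustration of size**

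Only the 42% comes from the documents (proportion prescribed an anti-diabetic at 1 year, used in the sample size section). The rest is assumed: no true ethnic difference; half of each group well engaged; an engagement-prescribing odds ratio of 1.5, 2 or 3; and recording probabilities r₁ (engaged) and r₀ (not engaged).

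Let p₁ and p₀ be the prescribing probabilities, with 0.5p₁ + 0.5p₀ = 0.42. Among recorded patients, P = (r₁p₁ + r₀p₀)/(r₁ + r₀), and the apparent odds ratio compares P between groups.

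Worked case, engagement odds ratio 2: p₁ = 0.5035, p₀ = 0.3365.
- Europeans recorded 60%/40%: (0.6 × 0.5035 + 0.4 × 0.3365)/1.0 = 0.4367.
- Minority group recorded 70%/70%: 0.4200.
- Apparent odds ratio = (0.4200/0.5800)/(0.4367/0.5633) = 0.93.

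| Recording, engaged/not engaged (European; minority) | OR 1.5 | OR 2 | OR 3 |
|---|---|---|---|
| 60/40; 60/40 (identical) | 1.00 | 1.00 | 1.00 |
| 60/40; 75/50 (minority higher by a common ratio) | 1.00 | 1.00 | 1.00 |
| 60/40; 70/50 (minority higher by a common 10 points) | 0.99 | 0.99 | 0.98 |
| 60/40; 70/70 | 0.96 | 0.93 | 0.90 |
| 60/30; 75/65 | 0.95 | 0.915 | 0.87 |

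With engagement in the model the odds ratio is 1.00 in every row. If the groups also differ in engagement (50% against 40% well engaged) but recording is 60/40 in both, omitting engagement changes the complete-case odds ratio by a factor of only 1.000 to 1.002 relative to the full population.

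In the 70/70 row the spurious differences are 1.0, 1.7 and 2.6 percentage points (0.4298, 0.4367 and 0.4461, each minus 0.4200). For scale, Table 1 lists 1.4 and 2.1 points as detectable for first-line metformin, a different outcome.

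**The case against.** **The adjustment is planned.** Engagement is inserted into the models for each outcome, so for the diabetes cohorts the estimate that the missing-data section relies on will exist. A reader might infer that the safeguard is absent altogether; the documents do not support that. The plan also names no base model as its headline result. What stands is that it never says which model the complete-case argument supports.

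**Leaving engagement out is a defensible choice of estimand.** If consultations partly mediate, adding them removes part of the total ethnic difference. This stands, and is a reason to keep the age-sex model, but that model is then outside the missing-data argument.

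**Sensitivity analyses exist.** HES-linked ethnicity (78% recorded), new registrants since 2006 (78%) and London practices (approaching 60%) are carried into the amendment, with baseline characteristics to be compared against the primary population. In the first two, missingness falls from about 50% to about 22%. They help, but none is said to add consultations to the model, and the plan acknowledges that they may introduce bias themselves.

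**Greater recording in minorities does not itself imply bias.** A reader might infer that it does. The common-ratio row shows otherwise, and the plan describes the effect of engagement as acting whatever the patient's ethnicity. The mechanism is possible but not documented.

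**The anchor is a drafting lag.** Section N says covariates come from the last entry before follow-up, and section O gives entry dates for the new cohorts. So it would be too strong to say the argument is beyond repair for people without diabetes. But the general rule does not override the explicit diabetes-diagnosis anchor for a one-year count, so the text needs changing.

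**Conclusion.** The point holds in this limited form. The complete-case justification covers one single-covariate model per outcome in the diabetes cohorts. It does not cover the base estimates, the unadjusted comparisons or the other single-covariate models, and as written it cannot be applied to the cohorts without diabetes.

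The size of any resulting bias cannot be derived from the documents. It depends on whether the engagement-recording link differs by ethnicity: negligible if the link is the same in all groups, and roughly 4% to 13% on the odds ratio in the two assumed scenarios where it differs most. Those figures illustrate the mechanism and do not estimate what this study will find. The gap in the plan is definite and its consequence uncertain, so the change should be made, but the planned analyses are not shown to be invalid.

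**What to change.** - Redefine the engagement covariate as the number of consultations in the year before each cohort's entry date: diabetes diagnosis, incident hypertension or raised blood pressure, or elevated CVD risk score.
- For every outcome and cohort, report the age, sex and consultations model beside the age-sex model.
- Keep consultations in the model when the other covariates are explored.
- State that only the consultation-adjusted estimates are supported by the complete-case argument, and that the age-sex estimate is kept as the total ethnic difference.

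The cost is one redefined variable and one extra model term. The downside is that consultations may partly mediate, which is why both estimates are shown.

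Inverse-probability weighting for recorded ethnicity is not a substitute. Ethnicity is the missing variable, so it cannot enter the weight model, and weighting then fails when recording depends on ethnicity. In a deliberately strong example, half of each group is engaged, prescribing is 50%/30% by engagement, Europeans are recorded 70%/30% and South Asians 70%/60%, and South Asians are 8% of the population.
- Unweighted: (0.7 × 0.5 + 0.3 × 0.3)/1.0 = 0.440 against (0.7 × 0.5 + 0.6 × 0.3)/1.3 = 0.408, an odds ratio of 0.876.
- Weighted: pooled recording is 0.70 if engaged and 0.92 × 0.30 + 0.08 × 0.60 = 0.324 if not. The proportions become (0.5 + 0.926 × 0.3)/1.926 = 0.404 and (0.5 + 1.852 × 0.3)/2.852 = 0.370, an odds ratio of 0.867.

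The bias remains, whereas consultations in the outcome model give 1.00.

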| List of Appendices Peer review process and outcome: Diabetes UK Sir George Alberti Clinical Training Fellowship award panel  Peer review process and outcome: LSHTM ethics board  Diagram of type 2 diabetes diagnosis adjudication algorithm for primary care records  Diabetes code list  Ethnicity code list  Medication for type 2 diabetes code list  Antihypertensive medication code list  Lipid-lowering medication code list  Covariates code lists:  coronary heart disease  cerebrovascular disease  heart failure  atrial fibrillation  hypertension  chronic kidney disease  peripheral arterial disease  retinopathy  neuropathy  cancer  COPD/ asthma  severe mental illness |

| **AMENDMENT – 9^TH^ DECEMBER 2019**  **(Highlighted text indicates new material)** |
| --- |
| Study Title (Max. 255 characters) Ethnic differences in the prescribing of anti-diabetic, antihypertensive and lipid-lowering medication for people with and without type 2 diabetes. |
| 1. **Lay summary (Max. 250 words)**     The UK’s South Asian and African Caribbean populations experience far higher rates of type 2 diabetes and its cardiovascular disease complications, e.g. heart disease and strokes, than European-origin (white) groups. Ethnic minority populations without diabetes also experience an excess of most types of cardiovascular disease. Control of blood glucose, high blood pressure and high cholesterol helps to reduce cardiovascular disease complications from diabetes. Despite this, we know little about ethnic differences in the use of medications which do this. Limited existing research suggests that both choice and effective use of diabetes, blood pressure or cholesterol-lowering medication may differ by ethnicity.  This study aims to compare use of these medications for people with and without diabetes of European, South Asian and African Caribbean origin. Using computerised medical records, the commencement, type, dose, monitoring and adjustment of medication will be studied, and reasons for differences sought.  By identifying ethnic disparities in the use of medications to control diabetes, high blood pressure and high cholesterol, we may highlight reasons for the excess of diabetes complications and cardiovascular disease seen in UK South Asian or African Caribbean groups. These findings may influence prescribing policies, and thus ultimately reduce ethnic differences in cardiovascular disease and complications of type 2 diabetes. |
| Technical Summary (Max. 300 words) UK South Asian and African Caribbean people with type 2 diabetes experience worse diabetic control and more cardiovascular complications than the European-origin population; ethnic minority populations without diabetes also experience an excess of most types of cardiovascular disease. Explanations are unclear. Blood pressure and lipid control, crucial to cardiovascular risk reduction for people with and without diabetes, also differ by ethnicity. However, ethnic differences in prescribing for diabetes, hypertension and hyperlipidaemia remain understudied.  Ethnic differences in prescribing anti-diabetic (in people with diabetes), antihypertensive and lipid-lowering medication (in people with and without type 2 diabetes) will be sought, including: i) time to commencement ii) choice of medication, iii) dosage, iv) monitoring and iv) time to intensification (either medication up-titration, addition or class switching) after detection of sub-optimal control.  Primary care electronic medical records will be used. Established algorithms and code lists will define ethnicity, diagnoses and medication use. Data will be analysed using Kaplan-Meier time-to-event methods and logistic, Poisson and Cox regression models (according to outcome), with South Asian or African Caribbean ethnicity as the exposure (baseline category=European). These methods will allow for differences in follow-up time. The potentially confounding or mediating influences of age, sex, smoking, BMI, deprivation, polypharmacy, multi-morbidity, drug adherence, patient engagement and diabetes duration/ HbA1c will be explored. |
| D. Outcomes to be Measured Proportion of people eligible for antihypertensive or lipid-lowering medication who are prescribed the respective medication; Time to first anti-diabetic/ antihypertensive/ lipid-lowering medication prescription; Choice of anti-diabetic/ antihypertensive/ lipid-lowering medication; Dose of anti-diabetic/ antihypertensive/ lipid-lowering medication; Monitoring of anti-diabetic/ antihypertensive/ lipid-lowering medication; Time to anti-diabetic/ antihypertensive/ lipid-lowering treatment intensification. |
| Objectives, Specific Aims and Rationale Overall aim  To investigate ethnic differences in prescribing for type 2 diabetes in UK primary care.  Objectives  For people of European, South Asian and African Caribbean origin, ethnic differences in the following will be investigated:   1. Proportions of people with: a) incident hypertension started on antihypertensives and b) an elevated 10 year CVD risk score (according to QRISK, ASSIGN, JBS2, Framingham or unspecified risk-estimating equations (26)) being commenced on statin treatment. 2. Time to initiation of first-line anti-diabetic/ antihypertensive/lipid-lowering medication 3. Choice of anti-diabetic (first- to third-line), antihypertensive and lipid-lowering medication 4. Doses used for each anti-diabetic, antihypertensive and lipid-lowering medication 5. Monitoring rate after medication commencement 6. Time to medication intensification (up-titration, addition or switching) after detection of sub-optimal control of diabetes, hypertension or blood lipids   Additionally, we will examine potential confounding or mediating role/s of:   1. Smoking, BMI, deprivation, polypharmacy, multi-morbidity, drug adherence (for objectives v) and vi)), patient engagement with healthcare, diabetes duration and HbA1c (in people with diabetes).   Null hypotheses   1. No ethnic difference in proportions of people started on a) antihypertensives or b) statin treatment will be detected. 2. No ethnic difference in time to initiation of first-line anti-diabetic, antihypertensive or lipid-lowering medication will be detected. 3. Regarding choice of medication: 4. No ethnic difference in the proportions of people prescribed metformin as first-line, or sulphonylureas, DPP4-inhibitors, thiazolidinediones, SGLT2 inhibitors, GLP1 agonists or insulin as second- or third-line diabetes treatment will be observed. 5. No ethnic difference in the proportions of people prescribed ACE inhibitors/ angiotensin-receptor blockers, calcium-channel blockers or thiazide diuretics for hypertension will be observed. 6. No ethnic difference in the proportions of people with ≥10% cardiovascular disease risk who are prescribed lipid-lowering medication will be observed. 7. No ethnic difference in the proportions prescribed the maximum dose of anti-diabetic, antihypertensive or lipid-lowering medication will be observed, and the modal dose for each class will not differ by ethnicity. 8. No ethnic difference in the monitoring rates of anti-diabetic, antihypertensive or lipid-lowering medication will be observed. 9. No ethnic difference in time to treatment intensification (after the detection of sub-optimal control) of anti-diabetic, antihypertensive or lipid-lowering medication will be observed. 10. Associations between ethnicity and prescribing will not be confounded or mediated by smoking, BMI, deprivation, polypharmacy, multi-morbidity, drug adherence, patient engagement, diabetes duration or HbA1c (in people with diabetes).   Rationale  Research indicates that control of diabetes and its allied cardiovascular risk factors is poorer in UK’s minority ethnic groups than in the background white population. Crucially, these discrepancies are likely to contribute to higher rates of heart disease and stroke, in people with and without diabetes, seen in these groups. By examining the associations above, this study seeks to determine whether ethnic differences in prescribing for people with and without diabetes are present, and explanations for them.  It is important to compare prescribing in people with and without diabetes for each ethnic group. Our previous work suggests that diabetes is a much more potent CVD risk factor in people of South Asian and African Caribbean-origin than those of European-origin, and differential prescribing of statins and anti-hypertensives in those with vs. without diabetes is a possible explanation for this.  If ethnic inequalities in prescribing are present, their identification may influence future prescribing recommendations and thus eventually lessen the personal and societal burden of diabetes and cardiovascular disease complications in ethnic minority groups. |
| Study Background The UK’s largest ethnic minority groups, people of South Asian and African Caribbean descent, are disproportionately affected by type 2 diabetes (1), and most types of cardiovascular disease (2). UKPDS (UK Prospective Study of Diabetes) established the importance of tight blood glucose control in reducing CVD complications (3), but research suggests that glucose control is poorer in UK South Asians and African Caribbeans than Europeans (4, 5), despite their greater prevalence of complications (2). Yet the use of anti-diabetic medication in these groups remains understudied. Blood pressure and lipid control is key in reducing CVD risk in people with and without diabetes (6), therefore we will also examine prescribing patterns for antihypertensives and lipid-lowering medication.  UK guidelines recommend metformin as first-line anti-diabetic therapy, with several choices of further agents before insulin use (7). A recent study has reported on the choice of second-line treatments in CPRD (8; ISAC protocol number 16_267), with some indication that people from ethnic minority groups are less likely to receive newer anti-diabetic drugs. However, the influence of key factors such as diabetes duration and adherence to treatment were not accounted for, and the related questions of monitoring frequency and expediency of appropriate treatment intensification were not studied. Moreover, evidence from smaller primary care databases suggests South Asians and African Caribbeans are less likely than Europeans to receive insulin, and more likely to be on a higher number of oral diabetes drugs (5, 9). UK hypertension guidelines advocate calcium-channel blockers (CCBs) as first-line treatment for African Caribbeans, and ethnic differences in monotherapy are established (10), but little examination of ethnic differences in prescribing exists beyond this. Studies from aggregated primary care data indicate that statins may be under-prescribed in areas with large ethnic minority populations (11, 12), but were limited by analysis at area level.  Delay in anti-diabetic treatment intensification is linked to poorer subsequent control (13), but in spite of the poorer diabetic control in ethnic minority groups, ethnic differences in time to intensification have never been studied. Equally, an absence of research on ethnic differences in intensification of antihypertensives exists (14). However, previous research indicates that African Caribbean people are less likely than their white counterparts to be prescribed statins (15), though it is unclear if this is the case for people with diabetes. Additionally, whilst evidence from CPRD indicates that hypercholesterolaemia with high cardiovascular risk is inadequately treated in people with diabetes (16), scrutiny by ethnicity is lacking. |
| Feasibility counts The primary analysis will be using data from CPRD alone (see section M for sensitivity analyses). Ethnicity recording for active patients is approximately 50% (17, 18). The ethnic breakdown is similar to that of the UK census 2011(20).  From 2000-2017, ≈280K patients initiated first-line and ≈80K second-line treatment for type 2 diabetes in CPRD (8). If 50% of these people had ethnicity codes present in their record, this would correspond to ≈140K starting first-line and ≈40K starting second line treatment. Using the 2011 census to calculate proportions, this would equate to ≈120.4K Europeans, ≈10.5K South Asians and ≈4.6K African Caribbeans initiating first-line treatment and 34.4K, 3.0K and 1.3K respectively starting second-line treatment. These are conservative estimates given the over-representation of ethnic minorities in the diabetic population.  Approximately 77% of the people with diabetes initiating first-line treatments are likely to be on antihypertensives (19), giving numbers for antihypertensive analyses of ≈92.7K Europeans, ≈8.1K South Asians, ≈3.5K African Caribbeans. Previous work in CPRD shows that ≈64% of people with type 2 diabetes receive statins (19), which will yield numbers for the lipid-lowering medication analyses of ≈77.1K Europeans, ≈6.7K South Asians and ≈2.9K African Caribbeans.  For people without diabetes, we expect approximately 219K people to initiate antihypertensive treatment over a similar study period to our own (20), equating to at least 94K Europeans, 6K South Asians and 3K African Caribbeans, once multipliers for ethnicity recording and the 2011 Census ethnicity breakdown are applied. From Chidwick et al (21), 113,035 people over 40 without a prior history of CVD had a high CVD risk score recorded between 2005-2013. Assuming 50% of these people had ethnicity recorded, and proportions by ethnicity are as per the 2011 census, this equates to approximately 49K Europeans, 3K South Asians and 2K African Caribbeans. |
